## APPENDIX G. RECOMMENDATIONS FOR INITIAL MANAGEMENT OF ELECTROLYTE IMBALANCES AND PREVENTION OF TUMOR LYSIS SYNDROME

### Initial Dosing for All Subjects

- Within the first 24 hours after the first dose of ABBV-467, if any laboratory criteria below are met, the investigator should be notified. No additional of ABBV-467 doses should be administered until resolution. A rapidly rising serum potassium is a medical emergency.
- Nephrology (or other acute dialysis service) should be available (per institutional standards to ensure emergency dialysis is available) for any subject hospitalized prophylactically or in response to laboratory changes.
- IV fluids (e.g., D5 1/2 normal saline) should be initiated at a rate of at least 1 mL/kg/hr rounded to the nearest 10 mL (target 150 - 200 mL/hr; not < 50 mL/hr). Modification of fluid rate should also be considered for individuals with specific medical needs.
- Monitor for symptoms or signs of TLS (e.g., fever, chills, tachycardia, nausea, vomiting, diarrhea, diaphoresis, hypotension, muscle aches, weakness, paresthesias, mental status changes, confusion, seizures). If any clinical features are observed, recheck potassium, phosphorus, uric acid, calcium and creatinine within 1 hour STAT.
- Vital signs should be taken at time of all blood draws or any intervention if TLS is clinically suspected.
- The management recommendations below focus on the minimum initial responses required. If a diagnosis of TLS is established, ongoing intensive monitoring and multi-disciplinary management will be per institutional protocols.

### Ongoing Dosing for All Subjects

- Management of electrolyte changes from last value at intervals > 24 hours after either the first dose is as below. Note: If any laboratory criteria below are met, no additional doses should be administered until resolution.
- For potassium, admit subject (if not already hospitalized) for any increase  $\geq 1.0$  mmol/L (1.0 mEq/L), or any level > ULN.
- Refer to the management guidelines for electrolyte changes observed within the first 24 hours after either the first dose or dose escalation (see below table).
- If a smaller potassium increase is observed that does not meet the criteria for admission above, recheck potassium, phosphorus, uric acid, calcium and creatinine in 24 hours and confirm no evidence of tumor lysis prior to further dosing.
- For uric acid, calcium, phosphorus and creatinine, refer to the management guidelines for electrolyte changes observed within the first 24 hours after either the first dose or dose escalation.

| Abnormality                                                                                                                          | Management Recommendations                                                                                                                                                                                                                                                                                                                                                                                                                                                                                                                                                                                                                                                                                                                                                                                                                                                    |
|--------------------------------------------------------------------------------------------------------------------------------------|-------------------------------------------------------------------------------------------------------------------------------------------------------------------------------------------------------------------------------------------------------------------------------------------------------------------------------------------------------------------------------------------------------------------------------------------------------------------------------------------------------------------------------------------------------------------------------------------------------------------------------------------------------------------------------------------------------------------------------------------------------------------------------------------------------------------------------------------------------------------------------|
| Hyperkalemia (including rapidly rising potassium)                                                                             |                                                                                                                                                                                                                                                                                                                                                                                                                                                                                                                                                                                                                                                                                                                                                                                                                                                                               |
| Potassium $\geq 0.5$ mmol/L increase from prior value (even if potassium WNL)                                                        | 
 
Recheck potassium, phosphorus, uric acid, calcium and creatinine in 1 hour STAT. If further <math>\geq 0.2</math> mmol/L increase in potassium, but still <math>< \text{ULN}</math>, manage as per potassium <math>\geq \text{ULN}</math>. Otherwise recheck in 1 hour.
 
Resume per protocol testing if change in potassium is <math>< 0.2</math> mmol/L, and potassium <math>< \text{ULN}</math>, and no other evidence of tumor lysis.
 
At discretion of investigator, may recheck prior to hospitalization. If stable or decreased, and still WNL, hospitalization is at the discretion of the investigator. Potassium, phosphorus, uric acid, calcium and creatinine must be rechecked within 24 hours.
 
                                                                                        |
| Potassium $> \text{ULN}$                                                                                                             | 
 
Perform STAT ECG and commence telemetry.
 
Nephrology (or other acute dialysis service) notification with consideration of initiating dialysis.
 
Administer Kayexalate 60 g (or Resonium A 60 g).
 
Administer furosemide 20 mg IV <math>\times 1</math>.
 
Administer calcium gluconate 100 – 200 mg/kg IV slowly if there is ECG/telemetry evidence of life-threatening arrhythmias.
 
Recheck potassium, phosphorus, uric acid, calcium and creatinine in 1 hour STAT.
 
If potassium <math>< \text{ULN}</math> 1 hour later, repeat potassium, phosphorus, uric acid, calcium and creatinine 1, 2 and 4 hours, if no other evidence of tumor lysis.
 
                                                                                                                       |
| Potassium $\geq 6.0$ mmol/L (6.0 mEq/L) and/or symptomatic (e.g., muscle cramps, weakness, paresthesias, nausea, vomiting, diarrhea) | 
 
Perform STAT ECG and commence telemetry.
 
Nephrology (or other acute dialysis service) assessment with consideration of initiating dialysis.
 
Administer Kayexalate 60 g (or Resonium A 60 g).
 
Administer furosemide 20 mg IV <math>\times 1</math>.
 
Administer insulin 0.1 U/kg IV + D25 2 mL/kg IV.
 
Administer sodium bicarbonate 1 – 2 mEq/kg IV push.
 
If sodium bicarbonate is used, rasburicase should not be used as this may exacerbate calcium phosphate precipitation.
 
Administer calcium gluconate 100 – 200 mg/kg IV slowly if there is ECG/telemetry evidence of life-threatening arrhythmias. Do not administer in same IV line as sodium bicarbonate.
 
Recheck potassium, phosphorus, uric acid, calcium and creatinine every hour STAT.
 
 |

| Abnormality                                                                                                                                                                                             | Management Recommendations                                                                                                                                                                                                                                                                                                                                                                                                                                                                                                                                                                                                                                                                                                                                                  |
|---------------------------------------------------------------------------------------------------------------------------------------------------------------------------------------------------------|-----------------------------------------------------------------------------------------------------------------------------------------------------------------------------------------------------------------------------------------------------------------------------------------------------------------------------------------------------------------------------------------------------------------------------------------------------------------------------------------------------------------------------------------------------------------------------------------------------------------------------------------------------------------------------------------------------------------------------------------------------------------------------|
| Hyperuricemia                                                                                                                                                                                    |                                                                                                                                                                                                                                                                                                                                                                                                                                                                                                                                                                                                                                                                                                                                                                             |
| Uric acid $\geq 8.0$ mg/dL (476 $\mu$ mol/L)                                                                                                                                                            | 
 
Consider rasburicase (prior to rasburicase administration please refer to local label for tests to be performed, contraindications and precautions. Dosing is per institutional guidelines). 
 
If rasburicase is used, sodium bicarbonate should not be used as this may exacerbate calcium phosphate precipitation.
 
 
 
Recheck potassium, phosphorus, uric acid, calcium and creatinine in 1 hour STAT.
 
                                                                                                                                                                                                                                                           |
| Uric acid $\geq 10$ mg/dL (595 $\mu$ mol/L)
or
Uric acid $\geq 8.0$ mg/dL (476 $\mu$ mol/L) with 25% increase and creatinine increase $\geq 0.3$ mg/dL ( $\geq 0.027$ mmol/L) from pre-dose level | 
 
Administer rasburicase (prior to rasburicase administration please refer to local label for tests to be performed, contraindications and precautions. Dosing is per institutional guidelines). 
 
If rasburicase is used, sodium bicarbonate should not be used as this may exacerbate calcium phosphate precipitation.
 
 
 
Notify nephrology (or other acute dialysis service).
 
Recheck potassium, phosphorus, uric acid, calcium and creatinine in 1 hour STAT.
 
If uric acid <math>< 8.0</math> mg/dL 1 hour later, repeat potassium, phosphorus, uric acid, calcium and creatinine 2 and 4 hours later, if no other evidence of tumor lysis.
 
 |
| Hypocalcemia                                                                                                                                                                                     |                                                                                                                                                                                                                                                                                                                                                                                                                                                                                                                                                                                                                                                                                                                                                                             |
| Calcium $\leq 7.0$ mg/dL (1.75 mmol/L)
and
Subject symptomatic (e.g., muscle cramps, hypotension, tetany, cardiac arrhythmias)                                                                    | 
 
Administer calcium gluconate 50 – 100 mg/kg IV slowly with ECG monitoring.
 
Telemetry.
 
Recheck potassium, phosphorus, uric acid, calcium and creatinine in 1 hour STAT.
 
If calcium normalized 1 hour later, repeat potassium, phosphorus, uric acid, calcium and creatinine 2 and 4 hours later, if no other evidence of tumor lysis.
 
Calculate corrected calcium and check ionized calcium if albumin low.
 
                                                                                                                                                                                                                                                                            |
| Hyperphosphatemia                                                                                                                                                                                |                                                                                                                                                                                                                                                                                                                                                                                                                                                                                                                                                                                                                                                                                                                                                                             |
| Phosphorus $\geq 5.0$ mg/dL (1.615 mmol/L) with $\geq 0.5$ mg/dL (0.16 mmol/L) increase                                                                                                                 | 
 
Administer a phosphate binder (e.g., aluminum hydroxide, calcium carbonate, sevelamer hydroxide, or lanthanum carbonate).
 
Nephrology (or other acute dialysis service) notification (dialysis required for phosphorus <math>\geq 10</math> mg/dL).
 
Recheck potassium, phosphorus, uric acid, calcium and creatinine in 1 hour STAT.
 
If phosphorus <math>< 5.0</math> mg/dL 1 hour later, repeat potassium, phosphorus, uric acid, calcium and creatinine 2 and 4 hours later, if no other evidence of tumor lysis.
 
                                                                                                                                                                          |

| Abnormality                       | Management Recommendations                                                                                                                                                            |
|-----------------------------------|---------------------------------------------------------------------------------------------------------------------------------------------------------------------------------------|
| Creatinine                 |                                                                                                                                                                                       |
| Increase $\geq$ 25% from baseline | 
 
Start or increase rate of IV fluids.
 
Recheck potassium, phosphorus, uric acid, calcium and creatinine in 1 – 2 hours STAT.
 
 |

ECG = electrocardiogram; IV = intravenous; STAT = statum (immediately); ULN = upper limit of normal;  
WNL = within normal limits

## APPENDIX H. MONITORING AND MANAGEMENT OF DRUG-INDUCED LIVER INJURY

Hepatic abnormalities will be graded based on the criteria in the table below, adapted from CTCAE v5.0.

| MedDRA SOC     | CTCAE Term    | Grade 1                                                                                               | Grade 2                                                                                              | Grade 3                                                                                            | Grade 4                                                                                    | Grade 5 |
|----------------|---------------|-------------------------------------------------------------------------------------------------------|------------------------------------------------------------------------------------------------------|----------------------------------------------------------------------------------------------------|--------------------------------------------------------------------------------------------|---------|
| Investigations | ALT increased | > ULN –
3 × ULN if
baseline was
normal; 1.5 -
3 × baseline if
baseline was
abnormal | > 3 - 5 × ULN if
baseline was
normal; > 3.0 -
5.0 × baseline if
baseline was
abnormal | > 5 - 20 × ULN if
baseline was
normal; > 5 -
20 × baseline if
baseline was
abnormal | > 20 × ULN if
baseline was
normal;
> 20 × baseline
if baseline was
abnormal | -       |
| Investigations | AST increased | > ULN -
3 × ULN if
baseline was
normal; 1.5 -
3 × baseline if
baseline was
abnormal | > 3 - 5 × ULN if
baseline was
normal; > 3 -
5 × baseline if
baseline was
abnormal     | > 5 - 20 × ULN if
baseline was
normal; > 5 -
20 × baseline if
baseline was
abnormal | > 20 × ULN if
baseline was
normal;
> 20 × baseline
if baseline was
abnormal | -       |

ALT = alanine aminotransferase; AST = aspartate aminotransferase; CTCAE = Common Terminology Criteria for Adverse Events; MedDRA = Medical Dictionary for Regulatory Activities; SOC = system organ class; ULN = upper limit of normal

An algorithm for monitoring and management of drug-induced liver injury in subjects with normal or elevated baseline ALT (defined as the average of 2 screening measurements) is presented in the table below.

| Treatment-Emergent ALT and/or AST | Treatment-Emergent TBL and/or INR                                            | Symptoms a | Action                                                                                                                                                                                                                                                                                            | Assessment/Management                                                                                                                                                                                                                                                                                                                                                              |
|-----------------------------------|------------------------------------------------------------------------------|-----------------------|---------------------------------------------------------------------------------------------------------------------------------------------------------------------------------------------------------------------------------------------------------------------------------------------------|------------------------------------------------------------------------------------------------------------------------------------------------------------------------------------------------------------------------------------------------------------------------------------------------------------------------------------------------------------------------------------|
| > 1 -
< 3 × ULN                | Normal
(TBL
< 2 × baseline in
subjects with
Gilbert
syndrome) | Absent                | 
 
Continue treatment; or consider holding treatment for concerning lab value trend
 
Monitor LFTs every 3 - 5 days
 
Follow-up for symptoms
 
                                                                                         | 
 
Rule out viral etiology, hepatic dysfunction related to underlying malignancy, and/or other drug-induced transaminase elevations
 
Consider ultrasound
 
Consider MRCP if ultrasound non-diagnostic
 
Limit/discontinue hepatotoxic medications (assess acetaminophen, dietary supplement, and alcohol use)
 
 |
| ≥ 3 -
< 5 × ULN                | Normal
(TBL
< 2 × baseline in
subjects with
Gilbert
syndrome) | Absent                | 
 
Hold treatment
 
Monitor LFTs every 3 - 5 days
 
Restart study drug at ≥ 33% dose reduction if LFTs return to baseline or < 3 × ULN (permanently discontinue treatment if LFTs become abnormal with treatment at reduced dose)
 
 |                                                                                                                                                                                                                                                                                                                                                                                    |
| ≥ 3 -
< 5 × ULN                | > 2 × ULN and/or
INR > 2.0                                                | Absent or
present  | 
 
Permanently discontinue treatment
 
                                                                                                                                                                                                               | 
 
Consider inpatient evaluation
 
                                                                                                                                                                                                                                                                                                    |
| ≥ 5 × ULN                         | Any                                                                          | Absent or
present  | 
 
Permanently discontinue treatment unless another etiology is identified and liver enzymes return to baseline
 
                                                                                                                                    | 
 
Monitor LFTs every 1 - 2 days
 
Consider hepatology consultation
 
                                                                                                                                                                                                                                                          |

ALT = alanine aminotransferase; AST = aspartate aminotransferase; INR = international normalized ratio; LFT = liver function test; MRCP = magnetic resonance cholangiopancreatography; TBL = total bilirubin; ULN = upper limit of normal

- a. Symptoms are defined as any constellation of right upper quadrant pain, swelling, and/or tenderness; marked fatigue; jaundice; nausea and/or vomiting; rash; eosinophilia; asterixis; and/or other symptoms that are consistent with symptomatic liver disease in the opinion of the treating investigator.

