#### Demographic and Laboratory Assessments

- ✓ 2. At least 18 years old.
- ✓ 3. Eastern Cooperative Oncology Group (ECOG) performance status 0, 1, or 2.
- ✓ 4. **Laboratory values** meeting the following criteria during the screening period prior to first dose of study drug:
  - For subjects with AML, the following hematologic parameter requirements are not applicable. For subjects with MM, subjects must have adequate hematologic function, defined as follows:
    - Absolute neutrophil count  $\geq 1000/\text{mm}^3$ ;
    - Platelet count  $\geq 75,000/\text{mm}^3$ ;
    - Hemoglobin  $\geq 8 \text{ g/dL}$ ;
  - Serum alanine aminotransferase (ALT)  $\leq 2.5 \times$  upper limit of normal (ULN);
  - Serum aspartate aminotransferase (AST)  $\leq 2.5 \times$  ULN;
  - Total bilirubin  $\leq 1.5 \times$  ULN (subject with documented Gilbert's syndrome may have a total bilirubin  $>1.5 \times$  ULN);
  - Amylase  $\leq 2 \times$  ULN;
  - Lipase  $\leq 2 \times$  ULN;
  - Creatinine clearance (CrCl)  $\geq 60 \text{ mL/min}$ , measured by 24-hour urine collection or calculated using the Cockcroft-Gault formula.
- ✓ 5. Echocardiogram with ejection fraction  $\geq 50\%$  and no other clinically significant finding that would increase the subject's susceptibility to cardiac toxicity.
- ✓ 6. No clinically relevant or significant ECG abnormalities, including ECG with QT interval corrected for heart rate (QTc) using Fridericia's formula (QTcF)  $> 450 \text{ msec}$  (males) or  $> 470 \text{ msec}$  (females).
- ✓ 7. Willingness and ability to comply with procedures required in this protocol.

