### Hepatic Laboratory Abnormalities

Subjects should be monitored closely for hepatic-related laboratory abnormalities and AEs. In instances of new observations of hepatic laboratory abnormalities (i.e., ALT and/or AST  $> 1- < 3 \times \text{ULN}$  and/or total bilirubin  $< 2 \times \text{ULN}$ ), clinical chemistries should be re-tested within 48 to 72 hours.

An algorithm for monitoring and management of drug-induced liver injury in subjects with normal or elevated baseline ALT and/or AST (defined as the average of 2 screening measurements) is available in [Appendix H](#) and should be used for study drug-related toxicity management. Guidelines should be followed for all subjects regardless of baseline liver function laboratory values. Hy's law is defined as ALT/AST and bilirubin in the normal reference range prior to study drug dosing, with subsequent development of ALT or AST  $\geq 3 \times \text{ULN}$  along with total bilirubin  $> 2 \times \text{ULN}$ , without findings of cholestasis

(elevated serum ALP) and with no alternative explanation. Any suspected cases of Hy's Law will require clinical review and confirmation.

Any increase in ALT and/or AST that is  $\geq 3 \times \text{ULN}$  but  $< 5 \times \text{ULN}$ , the dose will be held until the toxicity resolves to Grade 1 or lower, or to baseline if the toxicity was  $> \text{Grade 1}$  at the time of study entry. Upon toxicity resolution, the subject may restart study drug at a dose that is at least 33% lower than the previous dose. For ALT and/or AST increase  $\geq 5 \times \text{ULN}$  study drug may be restarted only if another etiology is identified and liver enzymes return to baseline.

In the event of hepatic abnormalities, documentation which captures relevant clinical signs and symptoms should be completed by the site in the source records and corresponding eCRF(s). In addition, for hepatic abnormalities, this should include imaging as clinically indicated (e.g., abdominal ultrasound, endoscopic retrograde cholangiopancreatography) to exclude alternative etiologies of liver injury (with full reports made available).

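### Appendix H gives opposite instructions for some subjects with Gilbert syndrome at ALT/AST 3 to <5 × ULN, because its two rows measure bilirubin against different references

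*Protocol*

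**What the plan says.** The algorithm in Appendix H has two rows for treatment-emergent ALT and/or AST of at least 3 and below 5 × ULN.

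- **Hold row.** The bilirubin cell reads "Normal (TBL < 2 × baseline in subjects with Gilbert syndrome" and symptoms must be absent. Treatment is held, and the action then reads "Restart study drug at ≥ 33% dose reduction if LFTs return to baseline or" below 3 × ULN.
- **Stop row.** The bilirubin/INR cell reads "> 2 × ULN and/or INR > 2.0", with symptoms absent or present. The action is to "permanently discontinue treatment". Gilbert syndrome is not mentioned.

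Criterion 4 in Section 5.1 limits total bilirubin to 1.5 × ULN, except that a "subject with documented Gilbert's syndrome may have a total bilirubin" above that level. No upper limit is stated for them.

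Section 6.2 (Hepatic Laboratory Abnormalities) directs sites to the Appendix H algorithm and adds: "Guidelines should be followed for all subjects regardless of baseline liver function laboratory values". The same section has its own rule for ALT/AST of 3 to <5 × ULN, which is to hold until resolution: "Upon toxicity resolution, the subject may restart study drug at a dose that is at least 33% lower than the previous dose". That rule does not refer to bilirubin.

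**The concern.** The hold row judges a Gilbert subject against that subject's own baseline, while the stop row judges everyone against ULN. If baseline bilirubin is above ULN, twice baseline is higher than 2 × ULN, so one laboratory picture can satisfy both rows. One row leads to re-treatment at a reduced dose and the other to permanent discontinuation. The Gilbert wording also appears in the row for ALT/AST below 3 × ULN, so the table evidently intends this group to be read against baseline. The stop row does not follow that reading.

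A smaller defect sits beside it. For subjects without Gilbert syndrome, the hold row ends at normal and the stop row starts above 2 × ULN, so the table has no entry in between.

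What is at stake is consistent safety handling across sites and, in some Cycle 1 cases, whether a subject counts as a DLT.

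**Working it through.** The documents give no figure to reproduce. The check applies the two rows literally, with bilirubin (TBL) and baseline b both in multiples of ULN, ALT/AST between 3 and <5 × ULN, INR not above 2.0, and symptoms absent.

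**Row conditions**
- Hold row, Gilbert: TBL < 2b. Hold row, others: TBL ≤ 1 (normal).
- Stop row, everyone: TBL > 2.

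**Overlap in Gilbert subjects.** Both rows apply when 2 < TBL < 2b, which is possible whenever b > 1. The protocol states no Gilbert baseline, so the values of b below are assumptions.

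| Assumed b (× ULN) | Upper end 2 × b | TBL meeting both rows (× ULN) |
|---|---|---|
| 1.0 | 2.0 | none |
| 1.2 | 2.4 | 2.0 to 2.4 |
| 1.6 | 3.2 | 2.0 to 3.2 |
| 2.0 | 4.0 | 2.0 to 4.0 |
| 2.5 | 5.0 | 2.0 to 5.0 |

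For example, at b = 1.6 a rise to 2.5 × ULN is below 3.2 (hold row) and above 2 (stop row).

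**Values in no row.** For non-Gilbert subjects, TBL above 1 and up to 2 × ULN meets neither condition. Test values of 1.1, 1.4, 1.5, 1.8 and 2.0 each returned no row. A Gilbert subject with b at or below 1 can also fall between the rows: at b = 0.8 the hold row ends at 2 × 0.8 = 1.6, so 1.8 has no row.

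**Section 6.2 alongside the table.** Its rule covers any ALT/AST of 3 to <5 × ULN. In the uncovered band it therefore supplies hold and reduce. Above 2 × ULN bilirubin it supplies the same action, where the stop row requires discontinuation.

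**DLT consequence.** Under Section 6.3, within the first 28-day cycle an AE of any grade that leads to discontinuation is a DLT, and so is any dose missed through toxicity not explained by the disease. Dosing is weekly.
- If a hold runs past the next Cycle 1 dose, the subject is a DLT under either row.
- If no Cycle 1 dose is missed, for example when the hold begins after the Day 22 dose, only the stop row produces a DLT. This assumes that no other DLT criterion is met, including that the bilirubin rise is not itself Grade 3 or higher; the document does not set out bilirubin grades.
- The Hy's law criterion does not settle the overlap cases, since its definition in Section 6.2 requires normal bilirubin before dosing and these subjects have b > 1.
- In Table 1 with 3 evaluable subjects, 0 DLTs means escalate and 1 means de-escalate.

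**The case against.** The strongest reply is that Section 6.2 already tells sites what to do throughout this ALT/AST band, so no subject is left without an instruction. For the uncovered band that stands, and a reader who infers that the protocol is silent there would be wrong. It does not help with the overlap. Section 6.2 has no bilirubin condition, so it cannot choose between the rows and contradicts the stop row itself.

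Three other limits also stand.

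- The bilirubin column is headed as treatment-emergent. A reader might infer that a Gilbert subject with b above 2 meets the stop row at baseline with no change, or that anyone enrolled between 1 and 1.5 × ULN starts in the uncovered band. The heading does not support either inference; only new rises count.
- The hold row requires absence of symptoms, and the footnote lists jaundice among them. The interval from 2 to 2b × ULN is therefore an upper bound, since a jaundiced subject meets only the stop row.
- A reader might infer that permanent discontinuation is always a DLT. Section 6.3 confines DLTs here to Cycle 1, and because a missed Cycle 1 dose is also a DLT, the two rows often give the same count.

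Gilbert subjects will also be few. That limits the frequency of the conflict without removing it.

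**Conclusion.** The point holds as a contradiction on the face of the table, with modest reach. For an asymptomatic Gilbert subject with baseline b above 1 × ULN, a treatment-emergent bilirubin between 2 and 2b × ULN calls for both restart at a reduced dose and permanent discontinuation. Criterion 4 expressly admits such subjects, and nothing elsewhere in the protocol resolves the conflict. The width of the band depends on b, for which the protocol gives no value.

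The missing row for non-Gilbert subjects is secondary: it is incomplete drafting of the table, for which the body text has a rule. The effect on BOIN decisions is narrow, arising mainly when a Cycle 1 hold causes no missed dose, but in a cohort of three a single such case can reverse the decision.

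**What to change.** The sponsor should reconcile the two Appendix H rows with each other and with the hepatic rule in Section 6.2. The result should be that each combination of ALT/AST and bilirubin leads to exactly one action, including for subjects with Gilbert syndrome and for non-Gilbert bilirubin above normal and up to 2 × ULN. Which action and which bilirubin reference apply is for the sponsor's hepatic safety experts; this review proposes neither.

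The cost is wording: the affected cells in Appendix H and the matching sentences in Section 6.2, changed together so that one is not left at odds with the other. No design, sample size or data collection changes.
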